### **C. Staff training.**

All research-engaged staff will be required to have completed CITI human subjects and Good Clinical Practice trainings, as well as training in study procedures. New research staff are required to observe the consent procedure for at least 3 subjects and have at least three of their initial attempts at the consent process observed by the research coordinator or an investigator before consenting independently. The Baystate Human Research Protection Program (HRPP) provides 1-on-1 training to orient new staff to working in research and has developed a competency-based manual for training research staff in proficiencies needed to function in clinical research roles. The HRPP training includes the following domains: Scientific Concepts and Research Design; Ethical and Participant Safety Concerns; Medicine Development and Regulation; Study and Site Management and Data Management and Informatics.

## D. Data Management and Analysis

**1. Data Acquisition, transmission, management and storage.** The study will involve audio-assisted computer-based interviews, and blood tests. We will deploy a modified version of the existing ACASI harmonized across the Rural Opioid Initiative UG3 sites to assess participants at baseline and follow-up. We will incorporate domains focused on HCV screening, confirmatory testing, and treatment experiences; telehealth exposure, experience, and satisfaction; additional measures focused on enhanced syringe access, sharing and injection-mediated risks; and experience and satisfaction with our mobile harm reduction and tele-care van. Final core survey questions will be harmonized with those decided upon by the UH3 National Executive Steering Committee. Survey domains that are already present include: sociodemographics; substance use; , injection behavior (including syringe sharing), sex risk behavior, overdose prevalence, substance use treatment, - and sexual-mediated risk behaviors; self-reported infectious disease and health status; access to harm reduction (e.g., SSPs, naloxone), medication for OUD (MOUD), and health care services; knowledge, attitudes, and experience with such services; geospatial locations of community assets, risks, and place of residence; mobile phone and texting practices and experiences; criminal justice involvement and egocentric and sociometric social networks. As in our UG3 project, the computer-based interviews will be conducted using a password-protected application on an encrypted, password-protected laptop computer in a private space with the participant wearing headphones.

All participants will have up to four follow-up visits at end-of-treatment (week 8 or 12 after treatment initiation), then 12, 24, and 36 weeks after end-of-treatment to monitor for reinfection. Respondents will complete the ACASI at each follow-up. These assessments will include an HCV-RNA viral load at each follow-up. If the dried blood spot testing is validated follow-up viral load testing will no longer utilize venipuncture to determine reinfection. Individuals who do not initiate HCV treatment will have follow-up visits timed as if they had started 8-weeks of treatment 8 weeks after T1. In other words, for those who do not initiate treatment, follow-up will occur 16, 28, 40, and 52 weeks after the T1 visit. Participants will receive \$30, \$30, \$40 and \$50, respectively, for completing the procedures at the four follow-up visits.

*Transmission* procedures will adhere to those specified by the Data Coordinating Center and the ESC. Analytic datasets will be stripped of patient identifiers, with re-identifying crosswalks kept in a separate, secure place. To protect against inappropriate access, we will first handle and transmit only de-identified data wherever possible. Data transmissions will be handled over secure VPN connections or other secure procedures, and data will be encrypted wherever feasible. Data forms and other records will be located in a secure environment with access restricted to authorized personnel, with backup copies kept in a separate, secure location.

*Data management and storage* must be secured against loss and inappropriate access. We will implement best-practice data collection and handling procedures, with well-documented procedures, and training and monitoring protocols that assure compliance with evolving federal and industry standards to protect identifying information and prevent breaches of confidentiality. Identifiers will be stripped and kept separate from the data in locked files available to only authorized staff; computers are encrypted and password-protected, and databases are password-protected as well. Electronic data back-ups will be performed at least daily. Data services will be provided by personnel located in the Epidemiology and Biostatistical Research Core at Baystate Medical Center.

**2. Data entry methods.** The study will involve audio-assisted computer-based interviews. All other data, including monitoring and scheduling data, will be entered through a secure, internet-enabled implementation of REDCap (Research Electronic Data Capture, Vanderbilt University). During recruitment and data collection, the database will be used to maintain contact rosters and provide prompts for multiple contacts. Multiple data views will be available to monitor recruitment and data completeness, so that problems can be pinpointed early and preventive action taken. Within the REDCap database, we will include date and time stamp fields for study process measures. During regularly scheduled staff meetings, we will review data on the process measures to

insure expected contacts and response times are met. Monitoring process measures will also enable us to identify and correct early any deviations in our enrollment and follow-up activities.

## **E. Quality Assurance & Regulatory Issues**

### **1. Quality assurance plan.**

Data Management will adhere to the highest standards of data quality and confidentiality.

*Data cleaning.* [name], [name] and [name] will ensure that all data are validated for completeness and consistency using checks for range and logical consistency. We will also work with the collaborative in data checking, cleaning, transmission and/or analysis; responding to inquiries from the ESC, the Data Coordinating Center (DCC) and Data Safety Monitoring Board (DSMB), and participating sites; compiling data for interim analyses as needed, and sending findings to appropriate entities. At regularly scheduled intervals defined by the ESC, study progress will reported to the ESC and DCC; the DSMB will receive data and reports quarterly. Our group uses REDCap for data management, and SAS and STATA as statistical packages; a REDCap-based tracking system also manages follow-up data collection and monitors data receipt.

*Missing data* may arise from subject dropout, non-compliance, or item nonresponse. Several approaches to assess the impact will be undertaken. In general, we will use all available data regardless of whether a patient has a complete record. Participants with missing data will be compared to those without to check for differences. We will explore missing data to evaluate the presence of patterns. Secondly, making the assumption that the data are missing at random (MAR), multiple imputation methods will be used to generate data for the missing values based upon the distribution of available data (using, such as, SAS PROC MI or Stata's MI IMPUTE), and results of multiple sets combined into a summary measure with appropriate statistical tests (SAS PROC MIANALYZE or Stata's MI ESTIMATE). Results from each strategy will be compared to analyses using the complete data.

### **2. Reporting mechanisms and timelessness for reporting of AEs/SAEs.**

An AE is defined as any unexpected reaction, side effect, or untoward event that occurs during the course of the trial. Staff will assess AEs by asking the following question at each contact: "Since we last met have you had any physical, emotional, mental, or behavioral problems or situations arise in your life that were problematic for you?" Stable chronic conditions that are present prior to study entry and do not worsen are not considered AEs. AEs and SAEs will be identified by a *proactive system of incident reports*, which are reviewed by the mPIs and staff, who will assign a classification to represent the event's documentation as an SAE and whether there is attribution to the study intervention or research procedures.

*The mPIs are responsible for ensuring that the Program Officer, IRB, and DSMB receive regular reports of SAEs, AEs, other unanticipated problems, and any modifications to study procedures or protocols.* Drs. [name] and [name] will ensure that all research staff are properly trained in the assessment of SAEs and AEs, and that a robust system of recording and reporting SAEs and AEs is in place and fully understood by research staff. The definitions of SAEs and AEs and procedures for reporting such events will be routinely covered during staff training; review and reinforcement of this information will be part of regular supervisory meetings, and AEs are a regular agenda item for project meetings. Research assistants will inquire about SAEs and AEs at each research interview, and will incorporate self-report to ensure timely identification of SAEs and AEs.

*Adverse events will be an agenda item at project meetings at least monthly.* Any adverse event that comes to the attention of the mPIs or the Project Director will be reported to the Baystate IRB, which will serve as the single IRB. Depending on the nature and seriousness of the adverse event, either the study protocol or the informed consent form may be changed, with the advice and approval of the Baystate IRB and NIDA. AEs will be reported to the NIDA PO at least once per year as a part of the annual progress report. At a minimum, this report will describe the event, when it occurred, the study arm of the participant, and the outcome/resolution. If

there were no AEs, a statement that no AEs occurred will be included in the progress report or communicated to the PO in writing.

All SAEs will be reported within 24 hours to the NIDA Program Officer, IRB and DSMB by email. This 24-hour notification will include a brief explanation of the SAE and when it occurred. A written follow up report will be sent within 72 hours of the event. The written follow up will include information on the date of the event, what occurred, actions taken by project staff, planned follow up (if any), the intervention group/study arm of the affected participant, whether the event appears to be related to the intervention, and whether participant will continue in the study). Based on the report, the DSMB will determine if sufficient evidence exists to qualify an SAE as requiring either further review, modification of the protocol, or suspension of data collection; it will issue such a report within 3 days of notification. The DSMB and IRB have the authority to suspend or terminate the research when the study intervention causes unexpected serious harm to participants. Resumption of data collection activities is contingent on resolution of the sources of the event and determination that the safety of participants will be assured if project resumes; concurrence among the DSMB, IRBs, Program Officers, Principal Investigator and local investigators will be communicated to NIDA. Changes that may need to be made to the protocol will be discussed with the NIDA Program Officer in advance. Agreed upon changes will be submitted as an amendment to the IRB and DSMB for approval. The mPIs will report such changes in the annual progress report to NIDA, along with analysis of cumulative SAEs and AEs to date.

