##### ***B. DSMB plan.***

A DSMB will be established to monitor the safety of the subjects, the study/data validity, the effectiveness of the medications under study, and any unexpected effects. The DSMB will ensure immediate and appropriate response to any sign of harmful effects with the potential to justify stopping study activities.

*Composition.* We propose a 3-person DSMB that includes a physician expert in addictions, an epidemiologist or biostatistician, and an individual representing the interests of the affected population. They will have neither professional nor financial interests in the study outcome, and will not be employed by the funding agency. Each member will bring expertise in the varied scientific disciplines needed to interpret the data and ensure participant safety. Resumes will be made available to the Program Officer and IRB.

*Charge.* The DSMB is charged with ensuring the safety of individuals participating in this study. Its activities will include reviewing any AEs or SAEs that occur, approving and overseeing the plan for interim data analysis,

and preparing written reports to inform the mPIs, as well as the Program Officer, of the impact of the research on the safety of the participants.

*Frequency of DSMB reviews.* The DSMB will meet via videoconference at the discretion of its Chair, but at a minimum 3 times – (1) prior to the commencement of data collection to review (and revise as necessary) the detailed DSMP (which will have been approved by the Program Officer and IRB), and ensure that a clear protocol for study monitoring is operational prior to data collection activities, (2) after the first 25% of subjects completes end-of-treatment assessment, and (3) after the first 50% subjects completes 12-week follow-up.

*Content of DSMB report.* The DSMB will send a report to the NIDA Program Officer within a month after each DSMB meeting, which will include meeting dates, meeting agenda and minutes, changes in membership (including qualifications and conflicts of interest for any new members), and DSMB recommendations for the study.

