#### **4. Potential risk and benefits for participants.**

For this study, AEs will include symptoms reported by the patient and abnormal measures of clinical importance noted by study staff. AEs will also include breaches of confidentiality; reports of current and/or intended physical harm to persons (including current and/or intended abuse of children or elders, or an investigation of such allegations(s)); as well as reports of discomfort from or dissatisfaction with assessment procedures, embarrassment in disclosing sensitive personal information, or dissatisfaction with intervention activities. Each AE will be classified by the study investigators as serious or non-serious and appropriate reporting procedures followed. For purposes of this data safety plan, SAEs are defined as any fatal event, any immediately life-threatening event, any permanent or substantially disabling event, and any event that results in hospitalization. Overall, direct-acting antiviral (DAA) regimens are extremely well tolerated, with only mild to moderate side effects. The most common adverse effects include headache, fatigue, diarrhea, nausea, pharyngitis, and insomnia, with fewer than 1% of patients in clinical trials stopping the medication because of adverse effects. Reactivation of hepatitis B virus (HBV) infection has been described during DAA treatment, thus this study will screen and exclude persons positive for HBsAg. Other than these risks associated with standard clinical care for HCV infection, the potential additional risk to study participants is minimal and includes breach of confidentiality and the discomfort of fingersticks and venipuncture. The benefits to participants include improved access to HCV virologic testing and effective treatment.

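### The AE definition in Data and Safety Monitoring section E.2 is worded for unexpected events and conflicts with section E.4, so known side effects could be counted inconsistently; the wording on suspension also needs reconciling

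*Protocol*

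**What the plan says.** All the relevant text is in the protocol's Data and Safety Monitoring part.

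- **Section E.2, definition:** "An AE is defined as any unexpected reaction, side effect, or untoward event that occurs during the course of the trial". Stable chronic conditions that predate entry and do not worsen are the only stated exclusion.
- **Section E.2, how AEs are elicited:** at each contact staff ask whether, since the last meeting, "have you had any physical, emotional, mental, or behavioral problems or situations arise in your life that were problematic for you".
- **Section E.2, use:** the AE and SAE definitions are covered in staff training. Incident reports are classified for seriousness and attribution, and AEs go into the annual progress report.
- **Section E.4, scope:** "AEs will include symptoms reported by the patient and abnormal measures of clinical importance noted by study staff". Reports of discomfort from assessment procedures are also included.
- **Section E.4, known effects of DAAs:** "The most common adverse effects include headache, fatigue, diarrhea, nausea, pharyngitis, and insomnia". They are described as mild to moderate. Hepatitis B reactivation is named as an effect already described, and is the reason HBsAg-positive people are excluded.
- **Section E.4, seriousness:** "Each AE will be classified by the study investigators as serious or non-serious and appropriate reporting procedures followed". "SAEs are defined as any fatal event, any immediately life-threatening event, any permanent or substantially disabling event, and any event that results in hospitalization".
- **Section E.2, stopping for harm:** the DSMB and IRB have "authority to suspend or terminate the research when the study intervention causes unexpected serious harm to participants". The sentence before it lets the DSMB decide, for any SAE, whether data collection should be suspended.
- **Section B, DSMB charge:** the board is to ensure "immediate and appropriate response to any sign of harmful effects with the potential to justify stopping study activities".

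**The concern.** An AE definition decides which events are recorded as AEs and so which appear in the safety reports. Expectedness is normally an attribute of an event once it has been recorded. Here it appears inside the definition, in the one sentence of the protocol that formally defines an AE. The protocol then names a set of DAA effects that are, by its own account, expected. Staff trained on E.2 could reasonably leave these out of the AE count, while staff following E.4 would put them in. The AE reports would then depend on which section a staff member had in mind.

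The same qualifier appears in the sentence on suspending or terminating the research. The neighbouring provisions on the DSMB's response to harm do not carry it, so the protocol describes the board's remit in more than one way.

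**Working it through.** No arithmetic applies. The check sets the sections side by side and asks how each treats the same event.

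**1. AE definition**

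| Event | Section E.2, plain reading | Section E.4 |
|---|---|---|
| Participant on a DAA reports nausea, a listed common effect | Expected, so not an AE | Patient-reported symptom, so an AE |
| Participant complains of discomfort from a blood draw, a risk that E.4 itself foresees | Expected, so not an AE | Discomfort from an assessment procedure, so an AE |
| Participant reports a symptom nobody anticipated | AE | AE |

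The sections agree on unanticipated events and disagree on foreseen ones. The second row shows that the conflict does not depend on the drug.

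**2. Which reading of E.2 is plain?** An adjective placed before a list usually governs the whole list. Section E.2 later groups SAEs and AEs with *other* unanticipated problems, which suggests that AEs were being thought of as one kind of unanticipated problem. The narrower reading, in which *unexpected* qualifies only *reaction*, is grammatically possible.

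**3. Does the definition carry into SAEs?** Section E.4 assigns seriousness to events that are already AEs, so a narrow AE definition could in principle carry through. Against that, the SAE definition is based on outcome and refers to any such event, and E.2 has every SAE reported within 24 hours. The carry-through is a possibility created by the wording. It is not a stated rule.

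**4. Suspension and termination**

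| Provision | Trigger | Condition of expectedness |
|---|---|---|
| Section B, DSMB charge | Any sign of harmful effects | None |
| Section E.2, sentence on DSMB review of an SAE | Any SAE; can lead to suspension of data collection | None |
| Section E.2, next sentence | Serious harm caused by the intervention; suspension or termination | Unexpected |

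Suspension of data collection is therefore available without the qualifier. Termination for harm is expressly granted only in the third provision, since the stopping rule in section E.6 covers efficacy and futility alone. The mismatch comes down to termination for a serious harm that was already known. The listed DAA effects do not test it, because they are mild to moderate and would miss a rule on serious harm by severity. Hepatitis B reactivation is the only named candidate.

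**The case against.** The strongest case on the other side is that this is a drafting slip with no operational effect.

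- *Unexpected* may attach only to *reaction*, which leaves side effects and untoward events unqualified.
- Section E.4 is worded specifically for this study and plainly includes reported symptoms.
- The question at each contact has no filter, and the review of incident reports has no expectedness step.

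Most of this stands as regards collection: no procedure in the protocol would discard a known side effect. It does not remove the conflict over classification. If the E.2 sentence can be read two ways, staff can be taught either, and only one agrees with E.4.

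On stopping, it can fairly be said that the sentence gives authority *when* unexpected serious harm occurs, not *only when*. Hepatitis B reactivation in a trial that excludes HBsAg-positive people might also itself be regarded as unexpected. Both points stand and leave only a narrow mismatch.

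A reader might infer three stronger conclusions, none of which the documents support:

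- **Known harms go unrecorded.** The open question and E.4 point the other way.
- **The DSMB cannot act on a known harm.** Section B and the SAE-review sentence in E.2 carry no such limit.
- **A countable number of events is lost, more in one arm than the other.** The protocol gives no rates for the listed effects. The trial is open-label and expects more DAA initiators in the mobile arm, but no described step sorts events by expectedness, so neither a number nor a direction can be derived.

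**Conclusion.** The point holds as an internal inconsistency in a core safety definition. On the plain reading, section E.2 excludes foreseen events that section E.4 expressly includes, and both sections govern the same reports. The consequence is possible inconsistent counting of known, mostly non-serious side effects. This rests on reading *unexpected* as governing the whole list; on the narrower reading the fault is ambiguity instead of contradiction, and the same edit cures it.

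No numerical size can be given. AEs are not among the listed primary or secondary outcomes, so no planned efficacy comparison is affected; what is at stake is the consistency of the safety reports. The suspension and termination wording is a separate, smaller mismatch that calls for reconciliation only.

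**What to change.** 1. Remove *unexpected* from the AE definition in section E.2 so that it agrees with section E.4.
2. If expectedness is wanted, record it as a separate classification on the incident report, beside seriousness and attribution.
3. Reconcile the E.2 sentence on suspending or terminating the research with the sentence before it and with the DSMB charge in section B. Which rule should apply is for the sponsor, DSMB and IRB to settle.

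The cost is a wording amendment, a matching line in staff training and, if item 2 is adopted, one form field. The existing question already elicits the events, so no new visits or data collection are needed. The small downside is more non-serious AEs in the reports.
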